## Abstract

**Introduction:**

Malaria in pregnancy remains a public health problem. The World Health Organization (WHO) recommends intermittent preventive treatment with sulfadoxine-pyrimethamine (IPTp-SP) to all pregnant women in moderate to high malaria transmission areas. Kenya's Ministry of Health recommends at least three doses of IPTp-SP (IPTp-SP3 +) to pregnant women in regions where malaria is endemic. Although SP remains cost-effective and effective for IPTp, there are two main challenges with the use of SP: i) widespread use of SP can lead to an increase in the prevalence of drug resistance molecular markers, including those encoding for
*Plasmodium falciparum* dihydrofolate reductase (
*dhfr*) and P
*f* dihydropteroate synthase (
*dhps*) and ii) SP, used either for curative or preventive treatment, is associated with microscopic and sub microscopic gametocytaemia, both of which contribute to sustained malaria transmission. Our study aims to investigate the dynamics of
*Plasmodium falciparum* gametocyte carriage in pregnant women under intermittent preventive treatment with sulfadoxine-pyrimethamine in Kilifi.

**Methods:**

This will be a cross-sectional study and will recruit (N=462) expectant women attending antenatal care (ANC) clinics in four health facilities within the Kilifi Health and Demographic Surveillance Sites: Njunju, Pingilikani, Ngerenya, and Kilifi County Teaching and Referral Hospital (KCTRH). To be recruited into our study, women will need to be in their first or second pregnancy when they are more likely to have malaria and should have had at least one dose of sulfadoxine-pyrimethamine.

**Expected application of results:**

Our study will provide information on the current status of malaria during pregnancy in Kilifi and the prevalence of gametocytes among expectant mothers on IPT-SP. The results of this study may help inform new interventions to prevent malaria during pregnancy, including adding a third drug to SP with probable gametocytocidal effects.

## Introduction/background

Malaria in pregnancy is a public health problem. According to the World Health Organization (WHO), 34% of pregnant women in the Africa region experienced malaria in 2023. Among the WHO subregions, the highest prevalence of malaria exposure during pregnancy was found in West Africa, while the lowest rates were observed in East and Southern Africa (
WHO, 2024). Malaria infection during pregnancy poses a substantial risk to the mother, fetus and newborn. The consequences of malaria in pregnancy include maternal anaemia, low birth weight, pre-term birth, stillbirth, and infant and maternal deaths (
McGregor *et al.*, 1983). In areas of stable malaria transmission, adults, including pregnant women, do acquire immunity to malaria and can, therefore, control but not clear malaria infections (
Takem & D'Alessandro, 2013). There are three strategies to combat malaria in pregnancy: intermittent preventive treatment during pregnancy (IPTp), insecticide-treated bed nets and prompt diagnosis and effective treatment. 'IPTp constitutes the administration—irrespective of parasitemia—of a curative treatment dose, usually sulfadoxine-pyrimethamine (SP) at predefined intervals, during routine antenatal care' (
Mockenhaupt *et al.*, 2008).

The WHO recommendation on IPTp-SP has undergone revisions. In 2004, the recommendation was a minimum of two doses of IPTp-SP during pregnancy. In 2012, the recommendation was changed to at least three doses of IPTp-SP. This was a result of supporting evidence that three doses of sulfadoxine-pyrimethamine were associated with higher birth weight and lower risk of low birth weight than the standard 2-dose regimens (
Kayentao *et al.*, 2013).In Kenya, the practice is the administration of three IPTp-SP doses (IPTp-SP3+) to pregnant women in regions where malaria is endemic. Over the last decade, most countries in sub-Saharan Africa have widely adopted IPTp-SP policies for pregnant women. However, there are wide disparities in utilizing the highly cost-effective IPTp-SP intervention. In a large cross-sectional analysis of 18,603 women (aged 15–49 years) from 8 African countries, the prevalence of 3 doses of IPTp-SP varied from 60% in Ghana to 31% in Sierra Leon (
Yaya *et al.*, 2018). In Kenya, the latest data indicate that the uptake of more than 3 doses of SP during pregnancy stands at 43% (
Miatu *et al.*, 2024). Some of the factors associated with the uptake of antimalarial drugs among pregnant women include the timing of ANC initiation, number of ANC visits, income level, a woman's educational level and stock-outs of the drugs (
Ameh *et al.*, 2016).

*Plasmodium falciparum* transmission from the human host to the mosquito requires the presence of infectious gametocytes in the human peripheral blood. Indeed, the probability that a mosquito will be infected depends, among other factors, on the duration, prevalence and density of gametocyte carriage in the human host (
Drakeley *et al.*, 1999). Highly effective antimalarial drugs target to restrain gametocyte carriage and reduce disease progression. Gametocyte carriage and infectivity to mosquitoes are consistently higher in drug-resistant parasites than in drug-sensitive malaria parasites, which fuels the spread of antimalarial resistance. This is because slower clearance and prolonged presence of asexual parasites associated with resistance increase gametocytogenesis (
Barnes & White, 2005). Of all the antimalarial drugs ever used, sulfadoxine-pyrimethamine has been associated with the highest prevalence and density of gametocyte carriage (
Targett *et al.*, 2001).

Reports of increasing resistance to SP are now threatening the effectiveness of IPTp-SP. Polymorphisms in the
*P. falciparum* dihydrofolate reductase/dihydropteroate synthetase (
*Pfdhfr/Pfdhps*) genes are known to be associated with high SP resistance and treatment failure, with parasites having the K540E mutation (a proxy for the
*Pfdhfr*–
*Pfdhps* quintuple mutant) linked with resistance rendering SP ineffective in clearing
*Pf* infections (
Desai *et al.*, 2016). On the other sextuple mutant parasites, quintuple mutant plus the additional
*Pfdhps* A581G mutation is associated with reduced IPTp-SP efficacy (
Naidoo & Roper, 2013).

A most recent study analysis of SP resistance over the last 25 years in Kilifi observed that the quintuple mutation form of sulfadoxine-pyrimethamine resistance witnessed a sustained increase over the years up to 83.6% in 2018 (
Omedo *et al.*, 2022). However, the Omedo
*et al.* study analysed samples from young children; therefore, it is unknown whether SP mutant parasites are also on the increase in pregnant women who continue receiving SP and that warranty investigation. There are conflicting data on the risks and benefits of IPTp-SP. Previous studies indicate that even if there is a rise in the prevalence of molecular markers of resistance among pregnant women, SP can effectively reduce the malaria burden during pregnancy and extend protection to non-malarial cases of low birthweight (
Taylor *et al.*, 2012). However, the SP, used for curative or preventive treatment, is associated with microscopic and sub-microscopic gametocytaemia, contributing to sustained malaria transmission (
Bousema & Drakeley, 2011). Furthermore, SP provides intermittent clearance or suppression of existing asymptomatic infections from the placenta and can prevent new infections for several weeks by maintaining suppressive drug levels (
Karunajeewa *et al.*, 2009). It is this prolonged clearance period for SP that drives gametogenesis.

Our study aims to understand the dynamic of gametocyte carriage in pregnant women under intermittent preventive treatment with sulfadoxine-pyrimethamine, specifically if the varying doses of SP influence gametocyte carriage. We will also assess SP resistance markers in women under IPTp-SP. To comprehensively understand the determinants of IPTp-SP uptake, we will utilize a dataset from a previous study, the Kilifi Perinatal and Maternal (KIPMAT) study. Previously, the data was used to assess the impact of IPTp-SP on birth outcomes (
Kamau *et al.*, 2023). In the present study, we will apply the logistic regression model to evaluate predictors of uptake of optimal doses of IPTp-SP.

### Rationale/justification

In malaria-endemic countries, the WHO recommends that pregnant women receive Intermittent Preventive Treatment with sulfadoxine-pyrimethamine (SP) during their antenatal care clinics (
WHO, 2014). SP works through two modes of action: i) treatment effect by clearing existing asymptomatic infections in the placenta and ii) prophylactic effect in which suppressive drug levels are maintained in the placenta for some time, and this prevents new infections from occurring (
White, 2005). IPTp-SP intervention faces two main challenges that hinder its effectiveness: first, emergence and widespread resistance to SP, and second, sub-optimal uptake of the intervention. Across various malaria epidemiological settings in Africa, there have been reports of polymorphisms in the
*P. falciparum* dihydrofolate reductase/dihydropteroate synthetase (
*Pfdhfr/Pfdhps*) genes, which are associated with a high-level of SP resistance (
Amimo *et al.*, 2020). Furthermore, parasites containing quintuple mutations, which is a combination of three
*dhfr* mutations (N51I, N59R, and S108N) and two
*dhps* mutations (A437G and K540E) and is a predictor of treatment failure have also been reported (
Kublin *et al.*, 2002). Although the percentage of women under IPTp-SP has increased over the years, uptake of the intervention has remained low (
Yaya *et al.*, 2018), The latest WHO World Malaria report indicates that although coverage of IPTp1, IPTp2 and IPTp3 increased, from 54%, 45% and 34% in 2021, to 64%, 54% and 42% in 2022, respectively, it fell short of the target of 80% (
World Malaria Report, 2023). Individual-level factors and healthcare challenges have been attributed to the varying IPTp-SP uptake (
Berchie *et al.*, 2024).

Kenya revised its guidelines to include IPTp3 doses around 2015 (
Kamau *et al.*, 2023). In a large study examining around 27,000 deliveries along Kenya's coastal region, an IPTp-SP dose response protection against low birth weight and stillbirths was observed (
Kamau *et al.*, 2023). Nevertheless, SP is associated with a high prevalence and density of gametocyte carriage. Therefore, our study proposes understanding the relationship between gametocyte carriage and the doses of SP among pregnant women in Kilifi. Additionally, we will assess the determinants of IPTp-SP intervention within our settings. Previous studies on SP mutations in Kenya have primarily focused on children (
Omedo *et al.*, 2022), with limited attention given to malaria in pregnancy.

### Null hypothesis

IPTp-SP does not drive gametocyte carriage in pregnant women.

### Study aim

Investigating the prevalence of
*Plasmodium falciparum*, drug resistance and gametocyte carriage in women under intermittent preventive treatment with sulfadoxine-pyrimethamine.

### Specific objectives

1) Determine the prevalence of
*Plasmodium falciparum* infections in pregnant women.2) Determine the prevalence of
*Pf* gametocyte carriage and its association with IPTp-SP doses in pregnant women in Kilifi3) Analyse the relationship between IPTp-SP doses and the frequency of SP-resistant parasites.

### Secondary objectives

a) To understand the factors affecting the uptake of three or more doses of IPTp-SP in Kilifi.b) Analyse SP resistance markers in expectant women under IPTp-SP

## Methods

### Study design

This will be a cross-section study to understand the dynamic of gametocyte carriage in women under IPTp-SP within Kilifi County.

### Study location

The Kenya Medical Research Institute, Centre for Geographic Medicine Research Coast (KEMRI CGMRC), will conduct the study. The study participants will be recruited from three dispensaries: Junju, Ngerenya, Pingilikani, and KCH Hospital. KCH is urban, while the other health facilities are located in rural settings. Recruitment will take place between February and August 2025.

### Study population

The aim is to recruit expectant women presenting at ANC clinics at KCH, Pingilikani, Ngerenya and Junju and within the Kilifi Demographic Health Surveillance Sites.

Study inclusion criteria

1) Women in their first or second pregnancies- who are likely to be infected with malaria due to their limited acquisition of immunity to malaria.2) Should have had at least one dose of SP

Study exclusion criteria

Expectant women with no documented evidence of SP dosage in their ANC bookletParticipants who refuse to consentWomen with obstetric complicationsExpectant women who are on malaria drugs or have been treated for malaria in the 2 weeks prior to the current ANC visitPregnant women on co-trimoxazole prophylaxis

### Sampling and recruitment procedures

Women who meet our study inclusion criteria and reside within the Kilifi Health Demographic and Surveillance Site will be recruited for our study. We will recruit participants from four health facilities: KCTRH, Ngerenya, Pingilikani and Junju. We will recruit expectant women during routine ANC visits at the four health facilities. We will approach and consent eligible participants after the attending nurse or clinician has seen them. The KEMRI CGMRC has had a long-standing engagement with these health facilities. As part of the study engagement activities prior to study imitation, we will request that the health facility allocate us a small room or space to set up a temporary room so we can confidentially consent our study participants and for other study-related activities. Since one of our eligibility criteria is that the expectant women should have had at least one dose of SP and the current guidelines state that "provision of SP should be done for above 13 weeks' of gestation", we anticipate recruiting women who will be attending their second or more ANC visits when standard antenatal care profile procedures (blood group, HB measurements, malaria test, blood glucose, syphilis, and urine protein etc) will have already been done. We cannot use this routine blood from the antenatal care profile procedures. However, if the participant is required to undergo an RDT malaria test as part of their routine care, we will only request an additional 0.35ml, collected using a fingerpick, from them if they turn RDT positive. We will collect blood for the RDT and the additional 0.35ml (if malaria-positive) only after the participant completes routine checks with the attending nurse. We anticipate that study participants will take approximately 1 hour to participate in our study procedures. Blood samples from study participants will undergo tests listed in
Table 1 below. We will collect the following demographic data from eligible study participants: mother's age, marital status, education level, parity status (based on parity and gravida), number of ANC attendance and number of doses of malaria prophylaxis.

**Table 1. T1:** Sample collection and laboratory procedures.

Goal	Laboratory procedures	Location	Volume of blood required
Rapid malaria detection	RDT	To be done at the ANC clinic	50ul
Presence or absence of malaria parasites	Microscopy (gold standard)	Additional blood samples will be shipped to KEMRI- CGMRC laboratories	50ul
Gametocyte carriage	qPCR		200ul
Detection of resistance to SP markers	DNA extraction, Sanger/NGS sequencing		100ul
Total blood volume			400 ul (0.4ml)

### Sample size

The minimum required base sample size using individual randomization (
Daniel, 1999):

$$n\geq \frac{Z_{\alpha /2}^{2}P(1-P)}{d^{2}}Deff$$

With P being the expected prevalence of malaria in the study area (in proportion to one) and d the required level of precision taken to be half of P here. Assuming a 7.1% malaria prevalence based on a previous study on malaria prevalence among adults aged 15–49 years in Kilifi (
Kamau *et al.*, 2020), we get a sample of size
*n* = 202 pregnant women, which after increasing by a design effect factor of 2 and 15% to take care of contingencies gives 475.

*Sample distribution across the study sites*

Kilifi County exhibits heterogenous malaria transmission 

Low transmission: Ngerenya (North) and Kilifi townModerate transmission: Pingilikani and Junju (South) (
Kimenyi *et al.*, 2022;
Mogeni *et al.*, 2016).

Given that gametocyte carriage varies with transmission intensity, age and recent malaria episodes and SP use (
Jafari-Guemouri *et al.*, 2018;
Muthui *et al.*, 2019; Stepniewska
*et al.*, 2008) and IPTp-SP use is uniform across the county, we will recruit proportionally from all sites (Pingilikani, Junju, Ngerenya, and Kilifi County hospital) until the target sample size (n = 475) is reached.

To understand the factors affecting the uptake of three or more doses of IPTp-SP in Kilifi, we will analyze surveillance data from the Kilifi Perinatal and Maternal (KIPMAT) study (
Seale *et al.*, 2015). The KIPMAT study was established at the Kilifi County Hospital in 2011 to standardize admission procedures to improve the clinical care for expectant women (
Seale *et al.*, 2015). It was a clinical surveillance study of pregnant women and their newborns. The study was embedded into the routine clinical care as a way of supporting and improving clinical care in resource limited setting. At admission for labour, all mothers were registered by trained fieldworkers. Data were collected on residential location, age, education level, gravidity, HIV status, ANC visits and SP frequency. At delivery, fieldworkers recorded information on delivery outcomes, sex, gestational age and infant weight. Data were saved onto the My Structured Query Language (MySQL) database.

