### Statistical analysis

Participant socio-demographic characteristics will be summarised by numbers and percentages if categorical. Continuous data will be summarised by mean, standard deviation (SD), and range if data are normally distributed and median, interquartile range (IQR) and range if data are skewed. We will summarise the prevalence of
*Plasmodium falciparum* infections and Pf gametocyte carriage in pregnant women, together with the associated 95% Agresti-Coull confidence interval. The Chi-square test will compare prevalence across groups (such as size and other characteristics). Regression analysis will be used to investigate factors affecting the uptake of three or more doses of IPTp-SP in Kilifi. Data will be analysed in version 17.0 (Stata Corp, College Station, TX), and graphs will be generated using R (
R Core Team, 2024). Furthermore, we will describe the relationship between IPTp-SP doses and the frequency of SP-resistant parasites.

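### The abstract gives a recruitment target of 462 and the Methods 475, and the sentence on the 15% allowance does not describe the step that yields 475

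*Protocol article*

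**What the plan says.** The protocol article gives its recruitment target in two places.

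- **Abstract, Methods:** "This will be a cross-sectional study and will recruit (N=462) expectant women attending". No derivation is given there.
- **Methods, Sample size:** the calculation is a single-proportion precision formula with a design effect. The prevalence is set as follows: "Assuming a 7.1% malaria prevalence based on a previous study on malaria prevalence among adults aged 15–49 years in Kilifi". The precision is "d the required level of precision taken to be half of P here". This leads to a base of "202 pregnant women", "which after increasing by a design effect factor of 2 and 15% to take care of contingencies gives 475". The paragraph on distribution across sites then says that recruitment runs "until the target sample size (n = 475) is reached".

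The Sample size section does not state the confidence level. The Statistical analysis section plans to report prevalence "together with the associated 95% Agresti-Coull confidence interval", so 95% is the natural reading.

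**The concern.** Two values for the planned number of women stand in the current text, and the article does not say how one relates to the other. The sentence that should explain the final figure does not settle the matter. It describes an increase of 15%, and the literal result of that operation on 404 is neither 475 nor 462.

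The planned number is what completed recruitment will be judged against. With two published values, a study that closed at 462 could be reported as having met the abstract's target while being 13 women short of the target in the Methods. A reader checking the calculation also has to guess how the contingency was applied. The possible cost in precision is that 462 may be too few to deliver the planned half-width once losses occur.

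**Working it through.** **Inputs**

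- P = 0.071 (Sample size section).
- d = P/2 = 0.0355 (same section).
- Deff = 2 and contingency 15% (same section).
- z = 1.96. This is an assumption, taken from the planned 95% intervals in the Statistical analysis section.

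**Step 1: base size**

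n = z² P(1 − P)/d² = 1.96² × 0.071 × 0.929 / 0.0355² = 201.06, rounded up to 202. The stated base reproduces.

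**Step 2: design effect**

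202 × 2 = 404. Without rounding the base first, 201.06 × 2 = 402.1.

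**Step 3: the 15% allowance, applied in the two usual ways**

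| Starting figure | Divided by 0.85 | Multiplied by 1.15 |
|---|---|---|
| 404 (base rounded to 202) | 475.3 | 464.6 |
| 402.1 (base unrounded, 201.06) | 473.1 | 462.4 |

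The Methods' 475 is the rounded base divided by 0.85, taken to the nearest whole number. The abstract's 462 agrees with the unrounded base multiplied by 1.15. The literal reading of the Methods sentence, the rounded base increased by 15%, gives 465 and matches neither published figure.

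**Step 4: size of the discrepancy**

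475 − 462 = 13 women, and 13/475 = 2.7%. Between 475 and the literal 465 the gap is 10 women, and 10/475 = 2.1%.

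**Step 5: what it means for precision**

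Half-width = 1.96 × √(2 × 0.071 × 0.929 / m), where m is the number of evaluable women after a 15% loss. The planned half-width is 3.55 percentage points.

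| Recruited | m = 0.85 × recruited | Half-width (points) |
|---|---|---|
| 462 | 392.7 (about 393) | 3.59 |
| 475 | 403.75 (about 404) | 3.54 |

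With a 15% loss, 462 misses the planned precision by about 0.04 points and 475 meets it. The unrounded requirement is 402.1 evaluable women, so 462 would still meet the target if losses stayed at or below 1 − 402.1/462 = 13.0%.

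**The case against.** The strongest reply is that the Methods section agrees with itself. It derives 475 and then names 475 as the end of recruitment, so anyone running the study from the Methods has one number. The 462 appears once, in the abstract, with no derivation and no rule attached. Dividing by 0.85 is the standard way to allow for losses, and describing it loosely as a 15% increase is a slip of wording. The precision at stake is about 0.04 percentage points, far less than the uncertainty in the planning values themselves: a prevalence taken from adults aged 15–49 and an assumed design effect of 2.

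Most of this stands, and it rules out two stronger readings. A reader might infer that 475 cannot be reproduced. It can, from the section's own inputs, as 404/0.85. A reader might also infer that the point at which recruitment stops is undefined. The Sample size section sets it explicitly at 475.

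The reply also limits what can be said about the origin of 462. The match with 201.06 × 2 × 1.15 is close, but the article never shows that calculation, and a figure left over from an earlier stage of planning would look the same. Likewise the article says only that the 15% is for contingencies. Treating it as loss of evaluable women is an interpretation, although it is the one that yields 475.

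The reply does not remove the contradiction. An article may condense a fuller protocol, but that does not account for two different values of its own planned number.

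**Conclusion.** The concern holds as a consistency error with a small numerical effect. The abstract's 462 and the Methods' 475 contradict each other and are not reconciled. The sentence leading to 475 describes an operation that would give 465. The 475 itself is sound under division by 0.85.

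The difference is 13 women. In the worst case considered, closing at 462 with a full 15% loss, the half-width would be about 3.59 points against the planned 3.55. That would not change any conclusion about prevalence. The result assumes z = 1.96, P = 7.1%, a design effect of 2, and that the 15% represents women who cannot be evaluated. It is a correction to make before the article is relied on, and it does not call the design into question.

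**What to change.** Two edits to the text:

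1. In the abstract, change 462 to 475 to match the Methods.
2. In the Sample size section, replace the clause on the design effect and contingency with wording such as: *202 × 2 = 404 evaluable women; allowing for 15% loss, 404/0.85 = 475.*

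The existing statement that recruitment continues to 475 can stay as it is. The cost is one line in each place, with no change to the design, the recruitment target in the Methods or the analysis.
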